## Interventions

*Therapist-guided ICBT.* Patients will receive 14 weeks of ICBT for OCD using a validated treatment protocol.(13-16) As in regular CBT for OCD, the main treatment component is exposure and response prevention (ERP). The therapists will be licensed psychologists with expertise in treating patients with OCD. Therapists will respond to messages encrypted in the Internet platform at a set time during office hours (8am-5pm) on weekdays, in order to ensure that participants receive a response within 24 hours. Each participant's response rate at the 3-month follow-up will be calculated and monitored by the project leaders. The participants who are non-responders (defined as Y-BOCS reduction < 35% and CGI-I >2)(30) at the 3-month follow-up will be contacted by telephone and offered face-to-face CBT for 14 weeks.

*Self-guided ICBT.* This arm will be identical to the ICBT described above but without any online therapist support. If participants experience any technical problems with the online platform during the treatment, they can contact project leaders for help. In the internet platform, patients will have detailed contact information in case of emergency. Participants in this group who are non-responders at 3-month follow-up will be offered up to 14 weeks of f2f CBT according to the same procedure explained in the previous section.

*Individual f2f CBT.* Patients receive 16 sessions of individual f2f CBT for OCD delivered over a time period of 14 weeks, according to a validated protocol.(31) Sessions will be held twice weekly during the first two weeks and once a week for the remaining 12 weeks. The therapists will be licensed psychologists with expertise in treating patients with OCD. The content of the f2f CBT is the same as in the ICBT arms. Sessions will be audiotaped in order to ensure that the therapists adhere to the treatment protocol. Adherence to protocol will be independently rated by a psychologist (not otherwise involved in the study) specialized in CBT treatment for OCD.

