### **Statistical analysis**

The main outcome analyses will be conducted according to the “intent-to-treat” principle. Mixed-effects regression analyses for repeated measures with maximum likelihood estimation (MLE) of parameters will be used with the assumption that data are missing at random. The latter assumption will be tested. For each outcome measure, the model will include fixed effects of time (baseline, mid-treatment, post-treatment, and 3-month follow-up [primary endpoint]), treatment group (guided ICBT, unguided ICBT, f2f CBT) and an interaction effect of treatment group x time to allow for the differential change between the three groups from baseline to the 3-month follow-up. The models will include individuals’ random intercept and random slope to account for variability between and within participants over time. Within- and between-group effect sizes will be calculated with Cohen’s *d*.(44) Numbers needed to treat will be calculated based on responder status.

Alpha for all analyses will be set at 0.05. Non-inferiority is established when the 90% Wald confidence interval for the difference between treatment conditions excludes the pre-specified margin of inferiority, which is set at 3 points on the Y-BOCS (45, 46). This means that if the upper limit of the 90% confidence interval is less than 3 points, we are 95% confident that ICBT will be non-inferior to f2f CBT. The non-inferiority hypothesis will be tested of both therapist-guided and self-guided ICBT against the f2f CBT. Additional analyses of the 12-month follow-up data will determine whether the treatment gains are maintained long-term and whether ICBT is non-inferior to f2f CBT at follow-up.

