### **Analysis of predictors and moderators**

We will analyse predictors and moderators of response and remission status at 3- and 12-month follow-up using repeated k-fold cross validation with 10 folds and 20 repeats to reduce the risk of model instability (49, 50). We then average model performance over the repeats using area under the receiver operating characteristic curve (AUC) of sensitivity and specificity to

distinguish between responders/remitters and non-responders/non-remitters (51).

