### Current trial status

Recruitment of participants started in September 2015 and the last participant is expected to reach the primary end-point (3-month follow-up) in February 2019. Primary data analysis will begin in April 2019. The naturalistic follow-up phase of the trial will continue until November 2019.

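### The secondary 12-month non-inferiority analysis is worded as ICBT versus f2f CBT, but by then non-responders in both ICBT arms have been offered f2f CBT

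*Combined protocol and SAP*

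**What the plan says.** The Statistical analysis section sets the non-inferiority rule: the upper limit of a 90% Wald interval must lie below 3 Y-BOCS points. The model's listed time points end at the 3-month follow-up, which is the primary endpoint. The section then says that further analyses at 12 months will settle two questions: if the gains last, and "whether ICBT is non-inferior to f2f CBT at follow-up".

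The Interventions section describes what happens between those two visits:

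- Guided ICBT: non-responders (Y-BOCS reduction under 35% and CGI-I above 2) "at the 3-month follow-up will be contacted by telephone and offered face-to-face CBT for 14 weeks".
- Self-guided ICBT: "Participants in this group who are non-responders at 3-month follow-up will be offered up to 14 weeks of f2f CBT".
- f2f arm: "Patients receive 16 sessions of individual f2f CBT for OCD delivered over a time period of 14 weeks". No further treatment is described for its non-responders.

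Analysis of predictors and moderators covers "predictors and moderators of response and remission status at 3- and 12-month follow-up". Current trial status states: "The naturalistic follow-up phase of the trial will continue until November 2019". Neither the Statistical analysis nor the Limitations section mentions the added f2f CBT, and no rule is given for Y-BOCS values recorded after it.

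**The concern.** The comparator is offered selectively, to ICBT patients who have not responded, before the 12-month comparison is made. A course of up to 14 weeks starting after the 3-month visit can finish well before month 12. Under intent-to-treat, the 12-month ICBT means then include patients who have also had f2f CBT.

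The contrast therefore answers a different question from the one in its wording. Maintenance of ICBT gains cannot be read from patients who were treated again. The shift also grows as ICBT performs worse, because more patients then qualify for the offer. At stake is a statement that ICBT is non-inferior in the long term, resting on a comparison that cannot separate ICBT from the f2f CBT that followed it.

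**Working it through.** **The plan's own error rate.** A two-sided 90% interval leaves 5% in the upper tail. With a true difference of exactly 3 and no added f2f CBT, P(declare non-inferiority) = Phi(-1.645) = 5%. A patient-level simulation (20,000 trials, 40 per arm) gave 5.0–5.4%.

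**Effect of the added f2f CBT.** Let p be the non-response share in the ICBT arm, u the uptake of the offer and g the mean Y-BOCS gain from the added course. The ICBT-minus-f2f difference falls by

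s = p × u × g.

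If ICBT alone is truly 3 points worse, the estimate centres on 3 − s. Non-inferiority is declared when the estimate plus 1.645 × SE is below 3, so

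P(declare) = Phi(s/SE − 1.645).

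**Inputs.** From the protocol: margin 3, 40 per arm, intercept variance 10.5, residual variance 20.4. The documents do not give p, u, g or a 12-month SD, so these are assumptions.

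- Low: 0.30 × 0.50 × 3 = 0.45 points
- Central: 0.40 × 0.50 × 5 = 1.0 and 0.40 × 0.75 × 5 = 1.5 points
- High: 0.60 × 0.80 × 7 = 3.36 points (0.50 × 0.90 × 8 = 3.6 combines three extremes)

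Standard errors: the protocol's intercept and residual variances give sqrt(2 × 30.9/40) = 1.24, ignoring the slope variance and dropout. An SD of 6 gives 6 × sqrt(2/40) = 1.34. The values 1.10 and 1.72 are assumed as outer bounds.

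| Shift s | SE 1.10 | SE 1.24 | SE 1.34 | SE 1.72 |
|---|---|---|---|---|
| 0.45 | 11% | 10% | 9% | 8% |
| 1.0 | 23% | 20% | 18% | 14% |
| 1.5 | 39% | 33% | 30% | 22% |
| 3.36 | 92% | 86% | 80% | 62% |

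**Simulation check.** Here f2f CBT was given only to ICBT patients with under 35% reduction (SD 6; the CGI-I part of the definition was not simulated). At a true difference of 3, ICBT non-response was 48%. With g = 5, uptake of 50% gave an observed difference of 1.79 and 24% false non-inferiority; uptake of 80% gave 1.06 and 45%. ICBT non-response rose from 29% at a true difference of 0 to 58% at 4.5, which confirms that the shift grows as ICBT does worse.

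**Why carrying the 3-month value forward is not a remedy.** It freezes patients selected for a poor score, while f2f non-responders keep their observed 12-month values. I simulated the protocol's variances (10.5, 0.04, 20.4) with assumed baselines of 24–26, mean reductions of 9–11, no true change after 3 months, and time coded by visit or by week. Selected non-responders improved by about 2 to 4 points through regression to the mean alone. At 50–75% uptake, carrying forward would penalise the ICBT arm mean by about 0.5 to 1.1 points, an error of similar order in the opposite direction.

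**The case against.** The strongest reply is that nothing central is damaged. The primary endpoint is at 3 months, the offer comes after that assessment, and the 12-month work is described as additional and the phase as naturalistic. This stands. A reader might infer that the trial's main non-inferiority conclusion is compromised. The documents do not support that: the primary test precedes the offer and its model stops at 3 months.

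Nor is the 12-month contrast invalid. Randomisation makes it a sound treatment-policy comparison of the sequence with f2f CBT. The defect is the label and the unstated estimand. The word naturalistic appears only under trial status and does not qualify the conclusion promised in the Statistical analysis section.

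The size is also open to challenge. The f2f content is stated to be the same as in the ICBT arms, so patients who did not respond to that content may gain little from it. The bar on other psychological treatment for OCD covers only the treatment period, so later care in the f2f arm is not excluded and would offset some of the shift. The protocol's silence does not show that f2f non-responders received nothing.

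Finally, one might infer that the cost-effectiveness analysis is wrong. The plan states no time horizon and already counts f2f session time and service use, so the added course can enter both cost and outcome. The predictor models are exploratory, include 3-month outcomes and test no non-inferiority. For both, the point is only what a 12-month result refers to.

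**Conclusion.** The point holds for the secondary 12-month analysis. As worded, a passed test would be reported as non-inferiority of ICBT, whereas the contrast supports only a statement about ICBT with f2f CBT offered to non-responders.

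The direction, towards non-inferiority for ICBT alone, rests on the added f2f CBT helping on average and on no comparable extra care in the f2f arm. The protocol's description of f2f CBT as the gold standard with documented efficacy makes the first plausible. The size is unknown: roughly 0.5 to 3.5 points under the assumptions shown. The central 1.0 to 1.5 points takes the 5% error to about 18% (SE 1.34) and 39% (SE 1.10) respectively; at the widest SE considered, 1.72, the same shifts give 14% and 22%. Severity: should-fix.

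**What to change.** Leave the offer of care as it is and change the analysis plan:

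1. In the Statistical analysis section, label the as-randomised 12-month comparison, and any 12-month statement on maintained gains, as ICBT with f2f CBT offered to non-responders versus f2f CBT. Record who starts the added f2f CBT and when, and report uptake by arm.
2. Base any 12-month claim about ICBT itself on a pre-specified analysis. Set Y-BOCS values after the start of added f2f CBT to missing and multiply impute them from baseline, in-treatment and 3-month data. Repeat with a stated range of delta penalties, for example from 0 up to the 3-point margin, and report the delta at which the conclusion changes. Do not carry the 3-month value forward.
3. Describe the 12-month response and remission predictor models, and any 12-month cost-effectiveness results, as referring to the sequence, with the cost of the added f2f CBT included.

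The cost is some plan wording, a record of f2f starts and one extra analysis. The 12-month claim about ICBT alone becomes weaker and depends on imputation assumptions. In the central case an arm has 40 × 0.40 = 16 non-responders; at 50–75% uptake only 8 to 4 of them remain without added f2f CBT to inform the imputation directly.

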### **Cost-effectiveness analysis**

Health economic data will be collected using the TIC-P(47) and the Swedish National Patient Register, the Swedish Prescribed Drugs Register and the longitudinal integrated data-base for health insurance and work-related research (LISA). Costs will be analysed using a societal perspective i.e. including both sick-leave, hospitalizations, service use, medication, etc. and analysed in relation to outcome (i.e. OCD symptoms and quality-adjusted life years using the Y-BOCS and EQ-5D, respectively). National tariffs will be used to estimate costs from health care visits. Productivity losses will be estimated using gross earnings data from each patient.(48) Treatment costs, i.e. therapist support time per patient logged on the platform and time spent on f2f sessions, will be included in the cost estimation.

Cost-effectiveness comparisons will be analysed using incremental cost-effectiveness ratios. The “net benefit approach” will also be used. This approach estimates the cost-effectiveness depending on different societal willingness-to-pay values for one unit of improvement.(48) Non-parametric bootstrapping (one thousand replications) will be used to estimate the difference between ICBT (guided or unguided) and gold standard f2f CBT.

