## METHODS AND ANALYSIS

### **Study design**

Single-blind, randomized controlled non-inferiority trial comparing therapist-guided ICBT, unguided ICBT without therapist support, and individual f2f CBT for OCD in adults. The total number of participants will be 120 (40 per group), with stratification according to source of referral (self- vs. clinic referred patients). Block randomization will be performed within each stratum to ensure all participants are equally represented across treatment conditions. Participants will be assessed at baseline, bi-weekly during treatment, at post-treatment, and at 3- and 12-months follow-ups. The CONSORT flowchart of the trial is depicted in Figure 1.

[figure not shown]

Figure 1: Participant flow in the study

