## Randomization and concealment

The randomization sequence will be generated by Karolinska Trial Alliance (KTA, <https://karolinskatrialliance.se>, an independent entity not involved in the study) before inclusion of the first participant, using masked block randomization. Patients will receive their randomization number based on the order of their first psychiatrist appointment. Patients will be stratified based on self- or clinical referral. Sealed envelopes with information on treatment allocation will be stored in a secure locker in case of emergency unblinding.

Assessors will be blind to group assignment up to the 12- month follow-up. To ensure that the blinding is maintained, patients will be given clear instructions not to disclose which treatment they have been randomized to while being interviewed by the blind assessors. Where blindness is inadvertently broken, raters will be immediately replaced and the participant re-assessed by another rater. Blind raters will be asked to guess each patient's group allocation at each assessment point.(29) This will establish if the blind raters' guesses regarding treatment allocation were better than chance.

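### The cost-effectiveness plan specifies no adjustment for baseline EQ-5D or baseline costs, although both are collected, so it gives up precision and leaves chance imbalance in the QALY estimate

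*Combined protocol and SAP*

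**What the plan says.** The section on cost-effectiveness analysis takes costs from the TIC-P and national registers, from a societal perspective. It relates them to OCD symptoms and "quality-adjusted life years using the Y-BOCS and EQ-5D, respectively". For the estimator it says "Cost-effectiveness comparisons will be analysed using incremental cost-effectiveness ratios", adds the net benefit approach, and continues: "Non-parametric bootstrapping (one thousand replications) will be used to estimate the difference between ICBT (guided or unguided) and gold standard f2f CBT". It names no regression model, covariate, QALY formula or time horizon.

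Table 2 (Measurements) schedules EQ-5D at screening, pre-treatment, post-treatment and both follow-ups. It schedules TIC-P at pre-treatment, post-treatment and both follow-ups. Study design gives 40 participants per group. On balance at entry, Randomization and concealment says "Patients will be stratified based on self- or clinical referral" and names no other factor.

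The mixed model under Statistical analysis has baseline as one level of time. Nothing carries that model over to an accumulated QALY or to costs.

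**The concern.** A QALY is normally computed as the area under the EQ-5D curve, and that curve starts at the baseline value. A baseline difference between arms therefore enters the QALY difference twice: directly through the first interval, and indirectly because patients who start higher tend to stay higher. Bootstrapping patients reflects this variability in the interval, but the centre of the bootstrap distribution keeps whatever imbalance the trial happened to have. Costs may behave similarly, since sick leave and productivity losses can differ between patients before treatment starts.

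Cost-effectiveness is secondary objective 3, and the Limitations section concedes that the trial may not be powered for it. Precision available from data already collected is worth having there. Leaving the choice open also allows adjustment to be decided after the imbalance has been seen.

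**Working it through.** The documents give no SD, target difference or power for QALYs or costs, so there is no figure of the plan's own to reproduce.

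**Inputs from the documents.** There are 40 per arm (120/3). Post-treatment is at week 15, and follow-ups are at 3 and 12 months.

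**Assumptions (not in the documents).** Follow-ups are counted from week 15, giving weeks 28 and 67. EQ-5D index SD is 0.15 to 0.25, equal at all visits. Between-visit correlation ρ is 0.4 to 0.7. QALYs are computed by the trapezoid rule.

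**1. Size of chance imbalance.** SE of a baseline mean difference = SD × √(2/40) = 0.224 SD. The chance that it exceeds 0.2 SD in either direction is 2 × [1 − Φ(0.2/0.224)] = 37%, for each baseline variable and each pairwise comparison. For EQ-5D, one SE is 0.15 × 0.224 = 0.034 to 0.25 × 0.224 = 0.056.

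**2. Horizon to week 28, constant correlation.**
- Trapezoid weights in years: 15/104 = 0.144 (baseline), 28/104 = 0.269 (week 15), 13/104 = 0.125 (week 28).
- QALY change per unit of baseline difference: b = 0.144 + ρ × (0.269 + 0.125) = 0.302 at ρ = 0.4 and 0.420 at ρ = 0.7.
- Shift from a one-SE imbalance: 0.302 × 0.034 = 0.010 to 0.420 × 0.056 = 0.024.
- Unadjusted SE = √(w′Rw) × SD × √(2/40), where R is the correlation matrix. w′Rw = 0.181 at ρ = 0.4 and 0.236 at ρ = 0.7, so the SE runs from 0.014 to 0.027.
- Share of variance removed by adjustment = b²/(w′Rw): 0.302²/0.181 = 50% and 0.420²/0.236 = 75%.

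**3. Horizon to week 67, constant correlation.** The weights become 0.144, 0.269, 0.500 and 0.375.
- b = 0.144 + ρ × 1.144 = 0.60 to 0.95.
- Shift 0.020 to 0.053; unadjusted SE 0.033 to 0.064.
- Variance removed 38 to 68%.

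**4. Correlation decaying by visit** (ρ, ρ², ρ³ at one, two and three visits apart).
- To week 28: b = 0.144 + 0.269ρ + 0.125ρ² = 0.272 to 0.394; variance removed 43 to 68%.
- To week 67: b = 0.356 to 0.706; variance removed 15 to 42%.

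| Horizon | Variance removed, constant ρ | Variance removed, decaying ρ |
|---|---|---|
| Week 28 | 50–75% | 43–68% |
| Week 67 | 38–68% | 15–42% |

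**5. Bias check.** In a simulation of 8,000 trials with 40 per arm, unadjusted and adjusted estimates both had mean error near zero. The SE ratio followed √(1 − r²), with r the baseline–outcome correlation: 0.867 simulated against 0.866 at r = 0.5, and 0.717 against 0.714 at r = 0.7.

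No calculation was made for costs, because nothing in the documents bounds the correlation between baseline and later cost.

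**The case against.** The strongest reply is that the section is silent rather than wrong. An ICER, the net benefit approach and a bootstrap are all compatible with covariate adjustment, and willingness to pay is framed per unit of improvement, which may point to a change score for the Y-BOCS. That stands: a reader might infer that the plan commits to an unadjusted analysis, and it does not. It leaves the matter unspecified, for QALYs and costs in particular.

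A reader might also infer that the unadjusted result is biased or its interval too narrow. Neither follows. Randomisation makes the unadjusted difference unbiased, and the bootstrap interval already contains the baseline variation. The shift in the working is a component of the reported SE, not an additional error.

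A third tempting inference is that imbalance could reverse the sign of the ICER or net benefit. The documents give no expected QALY or cost difference against which to judge that, so it is not claimed.

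Two further points stand. The week-67 figures depend on a horizon the plan does not state, and they cover a period in which ICBT non-responders have been offered f2f CBT. In addition, linear adjustment for skewed baseline cost can be sensitive to a few high-cost patients.

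What remains is that a more precise estimator is available from data already scheduled, and the plan does not specify it.

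**Conclusion.** The point holds as an omission that costs precision in a secondary analysis. On the stated assumptions, adjusting for baseline EQ-5D would cut the variance of the QALY difference by roughly half to three quarters at week 28 (43 to 68% with decaying correlation). At week 67 the gain is smaller and more uncertain, between 15 and 68% across both correlation patterns. It would also take out of the estimate a one-SE shift of 0.010 to 0.024 QALYs at week 28. These figures rest on assumed SDs, correlations, visit weeks and the trapezoid rule. The benefit for costs is plausible but unquantified. The validity of the unadjusted comparison is not in question.

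**What to change.** Add to the section on cost-effectiveness analysis that, within each bootstrap replicate (costs and effects resampled together within arm):
- QALYs are regressed on arm, baseline EQ-5D and referral stratum;
- costs are regressed on arm, baseline TIC-P cost and referral stratum;
- the adjusted differences are used for the ICER and net benefit.

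If the Y-BOCS ratio uses an endpoint or change score, include baseline Y-BOCS in that model too. State the QALY formula and time horizon, since the size of the gain depends on both. Report the unadjusted result as a sensitivity analysis, to guard against the influence of a few high baseline costs.

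This takes a few sentences in the plan and a few lines of code. It needs no new data or visits.

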## ARTICLE SUMMARY

- First study evaluating if two modalities of ICBT are non-inferior to the gold standard face-to-face CBT for OCD.
- Full health economic evaluation of therapist-guided ICBT, unguided ICBT and f2f CBT for OCD.
- Recruitment of both clinic-referred and self-referred patients, which will help generalise the results to more typical OCD cases.
- The exclusion of participants with certain diagnoses, e.g. people with Autism Spectrum Disorder, limits the generalizability.

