### *Secondary objectives*

2. To investigate if ICBT for OCD can be delivered without therapist support without impairing efficacy.
3. To determine if ICBT, compared to f2f CBT, is a cost-effective treatment for OCD.
4. To examine if there is a difference in treatment outcome between self-referred and clinically referred patients.
5. To explore predictors and moderators of treatment outcome as a first step towards personalized treatment selection.

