## CONCLUSION

OCD is associated with significant suffering, loss of function across multiple life domains, high suicide risk, and large societal costs. ICBT has great potential to increase access to evidence-based care for a large group of sufferers that normally do not receive evidence-based psychological treatments. The study outlined in this protocol is the first direct comparison of ICBT and gold standard f2f CBT and is a crucial step before ICBT can be recommended for use within the regular health-care system. The study will provide new insights into the effectiveness of different treatment modalities for OCD and the health economic evaluation will help decision-makers to rationally allocate available resources. Implementation of ICBT in regular healthcare would dramatically increase the availability of effective treatment to those suffering from OCD.

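### The economic plan specifies only contrasts with f2f CBT; without the guided-versus-unguided increment it cannot deliver the three-option evaluation that the protocol promises

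*Combined protocol and SAP*

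**What the plan says.** Secondary objective 3 is "To determine if ICBT, compared to f2f CBT, is a cost-effective treatment for OCD".

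The Cost-effectiveness analysis section has three method statements:

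- "Cost-effectiveness comparisons will be analysed using incremental cost-effectiveness ratios". No arms are named.
- On net benefit: "This approach estimates the cost-effectiveness depending on different societal willingness-to-pay values for one unit of improvement". Again no arms are named, and no range of willingness-to-pay values is given.
- Non-parametric bootstrapping with 1000 replications "will be used to estimate the difference between ICBT (guided or unguided) and gold standard f2f CBT". This is the only statement that names a contrast.

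Two other places set a wider scope. The Article summary announces a "Full health economic evaluation of therapist-guided ICBT, unguided ICBT and f2f CBT for OCD". The Conclusion says that "the health economic evaluation will help decision-makers to rationally allocate available resources".

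No part of the document plans an economic contrast between guided and unguided ICBT, an ordering of the arms by cost, a rule for dominated or extendedly dominated options, or a probability that a given arm is the best of the three.

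**The concern.** Guided ICBT, unguided ICBT and f2f CBT are alternative ways of delivering the same content (Interventions). A payer chooses one of them for a given patient. The useful increment for each option is therefore the one over the next best option still in contention, which need not be f2f CBT.

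The protocol gives reason to think that the gap between the two ICBT arms matters. The Interventions section gives f2f CBT 16 therapist sessions and gives unguided ICBT no online therapist support. The Introduction expects a fully unguided version to cost very little, and describes the evidence on leaving out the therapist as conflicting. Whether guidance is worth its added cost is thus an open question that the trial has the data to address. Objective 2 asks the efficacy half of it; the economic plan has no counterpart.

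At stake is how far the economic results can be used. Favourable results for both ICBT arms against f2f CBT would tell a decision-maker that either could replace f2f CBT. They would not say, with any measure of uncertainty, which one to fund.

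**Working it through.** The section states no power, probability or cost figure, so there is no figure of the plan's own to reproduce. The check asks how far the probability that guided ICBT beats f2f CBT can differ from the probability that it is the best of three.

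**Inputs.** Three arms of 40 (Study design). The documents give no unit costs, cost SDs, QALY means or QALY SDs. The main calculation avoids these by working in SE units. It assumes independent, normally distributed arm means of net benefit with equal variance.

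**Set-up.** Let F, G and U be the mean net benefits of f2f, guided and unguided, each with variance v. The SE of any pairwise difference is s = √(2v). Define

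- a = (true G − true F) / s
- d = (true U − true G) / s

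Then

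- P(guided beats f2f) = Φ(a)
- P(unguided beats f2f) = Φ(a + d)
- P(guided best of three) = Φ₂(a, −d; ρ), the bivariate normal probability with ρ = Cov(G − F, G − U) / (2v) = v / (2v) = 0.5

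**Results with a = 1.645, so that P(guided beats f2f) = 0.95**

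| Unguided relative to guided | P(unguided beats f2f) | P(guided best of three) |
|---|---|---|
| 2 SE better | Φ(3.645) = 1.00 | 0.02 |
| 1 SE better | Φ(2.645) = 1.00 | 0.16 |
| 0.5 SE better | Φ(2.145) = 0.98 | 0.31 |
| equal | Φ(1.645) = 0.95 | 0.49 |
| 1 SE worse | Φ(0.645) = 0.74 | 0.82 |
| 2 SE worse | Φ(−0.355) = 0.36 | 0.93 |

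In the equal case the two pairwise probabilities sum to 0.95 + 0.95 = 1.90. They are not shares of one decision and cannot be read as a ranking of three options.

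**Sensitivity to the strength of the pairwise result.** For P(guided beats f2f) of 0.90, 0.95 and 0.975, P(guided best) is 0.48, 0.49 and 0.50 if unguided is equal, 0.16 throughout if unguided is 1 SE better, and 0.79, 0.82 and 0.83 if it is 1 SE worse. The guided–unguided gap drives the result far more than the strength of the comparison with f2f CBT.

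**Illustration in money, all values assumed.** Mean costs are f2f 2000, guided 600 and unguided 100. Cost SD runs from 1000 to 3000, QALY SD is 0.05, and willingness to pay runs from 0 to 50000 per QALY.

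- Equal QALYs in all arms: P(guided beats f2f) is 0.95 to 1.00, while P(guided best) is 0.01 to 0.28.
- Unguided 0.01 QALY lower: P(guided best) is 0.01 to 0.50.
- Unguided 0.04 QALY lower, willingness to pay 30000 or more: P(guided best) is 0.81 to 0.99, close to the pairwise answer.

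**The case against.** The plan answers the objective as worded. Objective 3 asks about ICBT against f2f CBT, and the named bootstrap contrast matches it. This stands, and those comparisons should remain. The gap is against the scope set in the Article summary and Conclusion.

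A reader might infer that the plan uses the wrong comparator or rules out a three-way analysis. The documents do not support this. The ICER and net-benefit statements name no arms, and a net-benefit analysis can take three. What can be said is that no such comparison is specified. Nor is it certain that two separate differences are meant, because the wording about guided or unguided ICBT could describe a pooled arm. Pooling would hide the contrast further.

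A reader might also infer that the results would leave the arms unranked. That is too strong. The two differences share the f2f arm, so (G − F) − (U − F) = G − U gives the point estimate by subtraction. Its uncertainty does not follow from two separate intervals, because the differences are correlated through F.

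A third tempting reading is that guided ICBT is unlikely to be the best buy, or looks good only because f2f CBT is expensive. The documents support neither. They give no cost figures, and the societal perspective includes sick leave, hospitalizations and medication, so therapist time alone does not settle which arm costs most. The Introduction cites earlier literature in which supported patients did better; if unguided is clearly worse, the pairwise and joint answers agree.

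Finally, the section promises no acceptability curve or probability of being cost-effective. The probabilities above measure the gap between two questions. They are not outputs that the plan says it will publish. When the ICBT arms are exactly equal, a value of 0.49 describes a tie, and choosing either arm loses nothing.

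**Conclusion.** The point holds as a gap in scope. The contrast specified is sufficient for objective 3 and insufficient for the three-option evaluation and the allocation decision that the protocol says it will serve. A favourable result for guided ICBT against f2f CBT leaves its chance of being the best option anywhere from about 0.02 to 0.93, for unguided net benefit between 2 SE better and 2 SE worse than guided and a pairwise probability of 0.95. That range rests on normality, equal variance and independent arms; the money figures rest on assumed costs and QALYs. The documents do not show where in the range this trial lies. The primary non-inferiority analysis is unaffected. The change is worth making because the remedy is standard, uses the same data, and lets the trial say whether therapist guidance is worth its cost.

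**What to change.** In the Cost-effectiveness analysis section:

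1. Keep the comparisons of guided and unguided ICBT with f2f CBT as the answer to objective 3, and state that the two ICBT arms are not pooled.
2. Resample all three arms in each bootstrap replicate, so that every contrast comes from the same draws.
3. Report the guided-versus-unguided increment in cost, effect and net benefit, with its uncertainty.
4. Order the arms by mean cost, remove dominated and extendedly dominated options, and report sequential ICERs for those that remain.
5. For each willingness-to-pay value, report the probability that each arm has the highest net benefit, as three curves that sum to 1.

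The cost is slightly more analysis and one added paragraph, preferably settled before the economic results are seen. No further patients or data are needed. The headline for one ICBT arm may become less favourable. The warning under Limitations that the trial may lack power for the cost-effectiveness calculations still applies, including to the new increment.
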